## Abstract

**Background:**

Carpal Tunnel Syndrome (CTS) is the most common compressive neuropathy, accounting for 90% of all neuropathies. Its prevalence ranges from 3.8%–7.8% in the population. The gold standard for its diagnosis is the neurophysiological study (85% sensitivity and 95% specificity), with the disadvantage of being invasive, complex and expensive, which means an increase in cost and time for the diagnosis of the disease. The main objective of this diagnostic test evaluation study is to investigate the value of ultrasound in the diagnosis of CTS, and among the secondary objectives, to establish the ultrasound parameters that are predictors of CTS in comparison with neurophysiological studies, attempting to standardize a protocol and reference values that determine the presence or absence of CTS.

**Methods:**

Prospective, cross-sectional study. The reference test with which we compared the ultrasound is the neurophysiological test (NPT). Patients will come consecutively from the Neurophysiology Department of the Virgen Macarena Hospital, with clinical suspicion of CTS and fulfilling the inclusion/exclusion criteria. To calculate the sample size (EPIDAT program) we proposed a sensitivity of 78% and specificity of 87% with a confidence level of 95%, requiring 438 patients (264 NPT positive, 174 NPT negative). We followed an ultrasound study protocol that included the ultrasound variables: cross-sectional area at the entrance and exit of the tunnel, range of nerve thinning, wrist-forearm index, flexor retinaculum bulging, power Doppler uptake and the existence of adjacent wrists or masses. We propose a timeline for the study to be performed between 2020 and 2023. Finally, we propose a cost-effectiveness analysis.

**Discussion:**

Ultrasound not only allows to objectify the alterations of the median nerve but also the underlying pathological mechanisms in CTS. A multitude of ultrasound parameters have been described that should be regarded in syndrome’s study, among which we included the cross-sectional area, the range of nerve thinning, the wrist-forearm index, flexor retinaculum bulging, power Doppler uptake and assessment of anatomical alterations. The use of ultrasound as a diagnostic tool in CTS has many advantages for both doctors and the patients, as it is a non-invasive, convenient, and fast tool increasingly accessible to professionals.

**Trial registration:**

**Trials registry number**: NCT05556278.

## Introduction

### Background and rationale {6a}

The carpal tunnel is an anatomical space located at the base of the palm of the hand, delimited by a rigid floor and walls, the carpal bones, and a roof with a certain capacity for distension, the transverse carpal ligament or flexor retinaculum. The entrance of the tunnel is located between the scaphoid and pyramidal bones, and its exit between the trapezium and hamate bones. A number of anatomical structures pass through this relatively narrow space as it transitions from the forearm to the hand: the tendons of the superficial and deep flexor muscles of the fingers, the tendon of the long flexor muscle of the first finger, and the median nerve [1]. Thus, an increase in volume within this space, however small, can lead to compression of the nerve [2].

The dimensions of the carpal tunnel are 20 mm at the level of the hook of the hamate, narrow compared to the proximal (24 mm) or distal (25 mm) dimensions [3]. In healthy individuals the intratunnel pressure ranges between 3–5 mmHg in neutral position [4]; vascular compromise of the nerve begins when the pressure exceeds 20–30 mmHg [5], which could be favored by certain postures or gestures as common as using a computer mouse [6]. Adjacent musculature may also play a role in the etiology; in a cadaver study, the muscle belly of the flexor digitorum superficialis was observed to access the proximal tunnel during wrist extension, similar to the lumbrical muscles observed in contact with the distal tunnel during metacarpophalangeal flexion [7].

The median nerve is responsible for the sensory innervation of the first three fingers and the radial border of the fourth, which is why patients who suffer compression of the median nerve inside the tunnel report pain and hypoesthesia in these fingers. The palm of the hand, however, usually remains unaltered, as it is innervated by a sensory cutaneous branch that emerges 6 cm proximal to the entrance of the nerve into the tunnel [5].

Carpal Tunnel Syndrome (CTS) is the most common compressive neuropathy, accounting for 90% of all neuropathies [1,8]. It is estimated that 1 in 5 patients with symptoms of pain, paresthesia and numbness of the hand will be diagnosed with CTS based on examination and an electrodiagnostic test [8].

Its prevalence ranges from 3.8% to 7.8% of the general population, being more prevalent in females than in males (10% vs. 5.8%), with an incidence of 9.3 new cases per 100 persons per year [9,10]. It leads to increased absenteeism, morbidity and, depending on the country, a cost of up to 2 billion dollars per year [10].

It is characterized by a combination of motor and sensory symptomatology leading to functional impairment, manifested by weakness of the intrinsic hand musculature with decreased grip strength, pain and paresthesia [4]. The etiology of this entity remains uncertain, and most cases are labelled idiopathic; recently, magnetic resonance imaging, biomechanical and histological studies have proposed a close relationship between neuronal vascular dysfunction, synovial tissue, flexor tendons and their sheaths, with the onset of the syndrome [11].

Diagnosis has traditionally been established by anamnesis and physical examination; electrodiagnostic testing is frequently used as a method of confirmation and assessment of severity. Although these studies offer 85% sensitivity and 95% specificity [12], they have the disadvantage of being invasive and unpleasant for patients. Recent advances in ultrasonography techniques have considerably improved the quality of ultrasound imaging of the nerve while providing more compact and economical equipment that makes it more accessible to the clinician, making ultrasonography a potential tool for the evaluation of entrapment neuropathies.

The high prevalence of CTS in the general population causes a high demand for neurophysiological studies, which to date is considered the gold standard in its diagnosis; this leads to long waiting times for the test to be carried out as well as an increase in direct and indirect costs derived from the disease. The availability of an additional technique that allows CTS to be diagnosed quickly, non-invasively and inexpensively would represent a clear advance in healthcare and an improvement in the efficiency of the healthcare system. In this sense, the present study aims to investigate the usefulness of ultrasound in the diagnosis of CTS in comparison with the gold standard, the specific ultrasound parameters that predict the existence of the syndrome in comparison with neurophysiological studies, and thus try to standardize a study protocol and reference values that determine the presence or absence of the syndrome.

### Explanation for the choice of comparators {6b}

In our study, we included patients with CTS (confirmed by neurophysiological testing) and patients considered "healthy" (with negative neurophysiological testing), in order to analyze the ultrasound differences between the two groups.

## Objectives {7}

**Primary**: To assess the accurancy of ultrasound in the diagnosis of CTS with respect to nerve conduction studies.

Secondary:

To determine the set of ultrasound parameters (ultrasound standards and reference values) that best predict the existence of CTS.To evaluate the relationship between the intensity or degree of involvement between ultrasound findings and nerve conduction studies.To propose a standardised protocol for the study of CTS by ultrasound.To perform a descriptive cost-effectiveness analysis between ultrasound and neurophysiological studies in the diagnosis of CTS.To detect and describe qualitative anatomical alterations and pathological findings that could predispose to the presence of CTS.

**Hypothesis**: Ultrasound is more accurate than neurophysiological studies in the diagnosis of CTS.

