## Statistical methods

### Statistical methods for primary and secondary outcomes {20a}

After an initial exploration of the data, quantitative variables are expressed as means and standard deviations or medians and quartiles in case of asymmetric distributions, and qualitative variables as percentages.

The calculation of the measures of test accuracy of the ultrasound test as a diagnostic test for CTS: sensitivity, specificity, predictive values and likelihood ratios, are carried out considering the neurophysiological study as the reference test (gold standard).

Likewise, the reliability of the ultrasound is analyzed by calculating the degree of agreement between the diagnoses of the two tests using Cohen’s Kappa coefficient. The concordance of both tests with the established clinical severity is also studied.

The analysis of the quantitative variables did not present normality (Gaussian assumptions), therefore, for statistical inference, the Mann Whitney test (violations of Gaussianity) was used for independent quantitative variables. Shortly afterwards, a multivariate logistic regression model will be created to try to determine the best subset of them that predict CTS [20].

Finally, ROC curves will be performed to evaluate cut-off points for certain quantitative ultrasound parameters that discriminate well against CTS. In the ROC curves, the optimal cut-off point for greater sensitivity and specificity was determined by using the Youden index. In those ultrasound parameters where the ROC curve did not allow adequate discrimination, the median value of the data distribution was used.

In summary, the univariate analysis aims to identify which ultrasound parameters are related to the result of the CTS, thus providing elements of analysis to determine the cut-off points to be evaluated by means of ROC or medians, as well as the main variables to be considered in the multivariate model.

Data analysis is performed with SPSS 25.0 statistical software.

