The last two "items" that we analyzed in our study are, on the one hand, the search for anatomical alterations that may compress the median nerve as it passes through the tunnel (ganglions, tendonitis, etc.), since ultrasound allows easy detection of anatomical alterations of the nerve [36]. In our study, as described above, we performed a scan of the image in both the transverse and longitudinal planes, covering all structures from lateral to medial.

On the other hand, we assessed the presence of nerve grimacing in the longitudinal plane, to identify whether there is a specific point of compression. In general, the nerve increases in size immediately after the compression zone.

We have included the BCTQ scale, a validated, self-administered instrument that assesses the impact of CTS on both symptoms and patient function [49], and a statistically significant relationship has been demonstrated between CSA, NPT score, clinical symptoms and hand function [14,15]. Contrary to this, Mondelli et al. in 2008 [16] found no relationship when comparing the combination of ultrasound and NPT score versus BCTQ.

When comparing neurophysiological studies versus ultrasound, although the former offer 85% sensitivity and 95% specificity in the diagnosis of CTS, they are invasive and unpleasant for the patient [12]; recent literature has shown that patients themselves have a preference for ultrasound over nerve conduction studies [49].

Although the specificity of neurophysiological tests is high, there is significant variability in their sensitivity (56–85%) which can translate into false negative results between 10–20% of patients [33] and false positives between 16–34% [50]. Other authors report an NPT sensitivity of 88% and specificity of 93% [44].

Although ultrasound may not replace neurophysiological testing as the gold standard for confirmation, authors Fowler and Gaughan suggest that it could be proposed as a first-line tool [50]; they add that the best candidates for ultrasound are those with high prior probability based on examination and reported symptomatology. Several authors [33,51] propose ultrasound as an initial screening test, leaving nerve conduction for definitive diagnosis.

The use of ultrasound as a diagnostic tool in CTS has many advantages for both the physician and the patient. It is a non-invasive, convenient, and fast tool, and ultrasound equipment is becoming increasingly cheaper, making it more accessible to the healthcare system [21].

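### The hypothesis that ultrasound is more accurate than the neurophysiological test (NPT) cannot be tested while the NPT is the reference; any loss of apparent specificity is possible but of unknown size

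*Protocol article*

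**What the plan says.** - **Hypothesis** (Objectives {7}): "Ultrasound is more accurate than neurophysiological studies in the diagnosis of CTS".
- **Primary objective** (same section): "To assess the accurancy of ultrasound in the diagnosis of CTS with respect to nerve conduction studies".
- **Analysis** (Statistical methods {20a}): sensitivity, specificity, predictive values and likelihood ratios "are carried out considering the neurophysiological study as the reference test (gold standard". Cohen's kappa between the two tests, and the concordance of each with clinical severity, are added.
- **Groups** (Explanation for the choice of comparators {6b}): "we included patients with CTS (confirmed by neurophysiological testing"), set against "patients considered 'healthy' (with negative neurophysiological testing"). Eligibility criteria {10} require symptoms suggestive of CTS from every participant.
- **Quality of the reference**: "Although these studies offer 85% sensitivity and 95% specificity" (Background {6a}). The Discussion adds that "there is significant variability in their sensitivity (56–85"%), gives NPT false positives of 16–34%, and says: "Other authors report an NPT sensitivity of 88% and specificity of 93"%.
- **Sample size** {14}: expected ultrasound sensitivity 78% and specificity 87%, precision 5%, confidence 95%, giving 264 NPT-positive plus 174 NPT-negative patients, 438 in all.

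**The concern.** The hypothesis ranks two tests, while the design lets one of them define the disease. Every disagreement is then booked as an ultrasound error, so a claim of superiority over the NPT could never be earned from these data.

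A second issue follows. By the protocol's own figures the NPT misses some CTS. A symptomatic patient with CTS but a negative NPT enters the group called healthy, and a correct positive scan in that patient counts as a false positive. The Youden cut-offs and the logistic model are fitted to the same labels, so they learn NPT status, while the Abstract presents the resulting reference values as showing whether CTS is present.

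**Working it through.** **1. The plan's own figure.** For estimating one proportion, n = 1.96² × p(1−p) / 0.05².

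- p = 0.78: 3.8415 × 0.1716 / 0.0025 = 263.7, rounded up to 264.
- p = 0.87: 3.8415 × 0.1131 / 0.0025 = 173.8, rounded up to 174.

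The total of 438 reproduces. It is a precision calculation for ultrasound against the NPT; no comparison of two accuracies enters it.

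**2. Can the hypothesis be supported?** If CTS is defined as NPT-positive, the NPT has sensitivity and specificity of 100% by construction. Ultrasound reaches 100% only by agreeing with the NPT in every patient, which is a tie. Kappa is symmetric in the two tests and cannot say which is better. Clinical severity is not a diagnosis of CTS. No independent truth is defined.

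**3. How far could apparent specificity fall?** Inputs: NPT 85/95% (Background, Discussion) and ultrasound 78/87% (Sample size). Assumptions: 78/87% are true values, and the two tests err independently given true CTS status. With true prevalence π:

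- P = share of NPT-negatives with CTS = 0.15π / [0.15π + 0.95(1−π)]
- loss of apparent specificity = P × (0.78 + 0.87 − 1) = 0.65 × P

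| π | P | Loss (points) |
|---|---|---|
| 20% | 0.030/0.790 = 3.8% | 2.5 |
| 40% | 0.060/0.630 = 9.5% | 6.2 |
| 50% | 0.075/0.550 = 13.6% | 8.9 |
| 60% | 0.090/0.470 = 19.1% | 12.4 |
| 69.1% | 26.1% | 17.0 |

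The last row treats the planned split as a real NPT-positive share: 264/438 = 0.603, so π = (0.603 − 0.05)/(0.85 + 0.95 − 1) = 0.691. The loss passes 10 points only above about 53.5% prevalence. With NPT 88/93% and the same split, π = (0.603 − 0.07)/0.81 = 0.658, P = 0.199 and the loss is 12.9 points.

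**4. Correlated errors.** At π = 69.1% and NPT 85/95%, the 17.0-point loss becomes 11.0 with error covariances at 25% of their maximum and 5.1 at 50%. It disappears near 75%.

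**5. The 16–34% false-positive figure.** Read as 1 − specificity (an assumption), with NPT sensitivity 85% and the same split, NPT specificity of 84% gives losses of about 16 points in apparent specificity and 6 in sensitivity. At 66% they are about 13 and 18.

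**6. Feasibility.** NPT sensitivity 56% with specificity 95% and a 60.3% positive share gives π = 0.553/0.51 = 1.08, which is impossible. Not every combination of quoted values fits the planned split.

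**The case against.** The strongest reply is that only one sentence is wrong. The primary objective, sample size and main accuracy analysis consistently target ultrasound against the NPT, and that target can be met. The Discussion admits the NPT's limits and says ultrasound may not replace it, and the protocol puts the word healthy in quotation marks. All of this stands, and it confines the defect to the hypothesis and the group label.

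A reader might infer that specificity will drop by more than 10 points. The documents do not support that, for three reasons:

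- **Prevalence is not given.** The 264:174 split comes from the precision formula, and patients are appointed until both groups are full, so it need not mirror the clinic. The Background's 1-in-5 figure would put the loss near 2.5 points. That figure concerns hand symptoms in general, however, and the Sample size section describes high clinical suspicion. At 20% prevalence the NPT-positive share is 0.20 × 0.85 + 0.80 × 0.05 = 21%, so 264 positives would need about 264/0.21 ≈ 1,257 consecutive patients. A higher prevalence fits the plan better but is not established.
- **Independence is doubtful.** The Discussion says early disease may look normal on ultrasound. If the NPT also misses early cases, the errors correlate and the loss shrinks.
- **78/87% may already be measured against the NPT.** The Sample size section introduces them for that comparison, and the Discussion does not name the source study's reference. If so, lowering them again counts reference error twice.

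For the same reasons it would be wrong to infer that 174 negatives miss the ±5-point precision.

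**Conclusion.** The hypothesis contradicts the primary objective beside it and the analysis plan. This follows from the definitions alone, needs no numerical assumption, and must be corrected. The primary objective remains answerable and the sample size is right for it.

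Downward bias in apparent specificity, relative to true CTS status, is a real possibility given the protocol's own NPT error rates, but its size is conditional. Under independent errors, NPT 85/95% and a true 78/87% ultrasound, it runs from about 2.5 points at 20% prevalence through 9 at 50% to 17 at 69%, and less if errors are positively correlated. The protocol gives neither the prevalence nor the correlation, so no single figure should be quoted as the expected loss.

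**What to change.** 1. **Restate the hypothesis** as estimating the sensitivity and specificity of ultrasound against the NPT, expected at 78% and 87%, with a 95% confidence half-width of about ±5 points. Set no pass/fail margin: at n = 174, 151 correct negatives give an interval of 81.7–91.8% and 152 give 82.4–92.3%, so neither fits inside 82–92%.
2. **Drop any claim of superiority** over the NPT.
3. **Rename the comparison group** NPT-negative symptomatic patients, wherever it is now called healthy.
4. **Optionally, add a labelled sensitivity analysis** for reference-standard error. It should vary NPT sensitivity and specificity over feasible combinations of the quoted values (including the 16–34% false-positive figure), prevalence and error correlation. It should not presume Tinel and Phalen results as extra indicators: they are described under data collection {18a} but absent from the variables listed under Outcomes {12}.

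Items 1 to 3 cost only rewording. Item 4 needs no new data, but its results rest on assumptions these data cannot check, so it stays secondary. The sample size needs no change.

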## Trial design {8}

Prospective, cross-sectional study that compares electroneurography and ultrasound in the diagnosis of CTS. Also, a cost-effectiveness analysis will be proposed to evaluate the costs of the consumables established by the Andalusian Health Service used in both tests and the average time for each of the tests, in order to calculate the cost of the professional when performing each of them.

## Methods: Participants, interventions and outcomes

### Study setting {9}

We compared the NPT based on the recommendations of the American Association of Electrodiagnostic Medicine (AAEM) protocol with the ultrasound study protocol described in Chen et al. [10] for assessing its effectiveness. The study protocol included different variables: cross-sectional area at the entrance and exit of the tunnel, range of nerve thinning, wrist-forearm index, flexor retinaculum bulging, power Doppler uptake and the existence of adjacent wrists or masses.

Patients will come consecutively from the Neurophysiology Department of the Virgen Macarena Hospital in Seville (Spain), with clinical suspicion of CTS and fulfilling the inclusion/exclusion criteria. Electroneurography or ultrasound diagnosis techniques will be performed to compare their effectiveness. This study has been approved by the Andalusian Biomedical Research Ethics Committee (Comité de Ética de la Investigación Biomédica de Andalucía) on August 3^rd^, 2020 (a462739eb0fd339704749b3269feed7855a3aecd).

### Eligibility criteria {10}

We establish the following inclusion criteria in order to be able to take part in the study:

Presenting clinical symptoms suggestive of CTS, at least one of the following:
Neuropathic profile pain in wrist-hand at the level of the median nerve territory (wrist, first-second-third, and radial half of the fourth finger by palmar and/or volar side), possibility of irradiation of the pain towards the forearm and/or arm.Nocturnal symptoms.Hypotrophy or atrophy of the thenar eminence.Self-described sensory alteration (sensation of cramping, numbness, tingling, hypoalgesia or analgesia).Age: 18 to 75 years.Consent to participate in the study.

Similarly, the exclusion criteria established are as follows:

Previous surgery on the wristAcquired or hereditary pathology causing peripheral neuropathiesPolyneuropathy of any etiologyRheumatoid arthritisDiabetes Mellitus

## Interventions

### Intervention description {11a}

We work side by side with the neurophysiology service of the Virgen Macarena hospital (Seville, Spain); they will apply the neurophysiological evaluation protocol between 1 and 3 months previous to the echography study.

**Neurophysiological**:

The neurophysiological evaluation protocol is based on the recommendations of the AAEM [12], listed in Table 1.

**Table 1 pone.0281221.t001:** Recommendations of the American Association of Electrodiagnostic Medicine (AAEM).

PROTOCOL FOR NEUROPHYSIOLOGICAL STUDY ACCORDING TO AAEM [12]	
**Parameter 1**	Performing median motor conduction velocity with surface electrodes (recording on abductor pollicis brevis-APB- and reference along the distal tendon-extremus thumb). Bipolar electrode stimulation at wrist and elbow. Calculation of distal motor latency (DML), motor conduction velocity (MCV) wrist-elbow. Assessment of amplitude and duration of the potentials obtained.
**Parameter 2**	Ulnar motor conduction velocity with surface electrodes (recording in the hypothenar eminence and reference along the distal tendon-extremus-fifth finger). Bipolar electrode stimulation at wrist and elbow (inferior-superior). Calculation of distal motor latency, motor conduction velocity wrist-lower elbow and lower elbow-upper elbow. Assessment of amplitude and duration of the potentials obtained.
**Parameter 3**	Orthodromic median sensory conduction with stimulation on 2 and 4 fingers and palm and recording on wrist. Stimulation on 3 fingers and recording on palm. Assessment of sensory conduction velocity (SCV) in the 2 finger-wrist, 4 finger-wrist, palm-wrist and palm-wrist segments. Assessment of amplitude and duration of the potentials obtained.
**Parameter 4**	Ulnar orthodromic sensory conduction with stimulation on 4 and 5 fingers and recording at the wrist. Assessment of conduction velocity in the 4-wrist and 5-wrist segments and amplitude and duration of the potentials obtained. Comparison of the IV middle finger-ulnar.
**Parameter 5**	Orthodromic radial sensory conduction with stimulation of the dorsum of the MCF joint of 1 finger and recording on the radial edge of the forearm. Assessment of conduction velocity and amplitude and duration of the potentials obtained.
**Parameter 6**	Antidromic sensory conduction of median, ulnar and radial with surface electrode recording at the base of 2 and 4 fingers (median), at the base of 4 and 5 fingers (ulnar) and at the dorsum of 1 finger MCF (radial) with stimulation at the wrist for median and ulnar, and at the radial edge for radial.

